Given the importance of oxidative stress capacity, many compounds have been developed to induce NRF2 and build the capacity to defend oxidative stresses in different disease setting. For example, sulforaphane [1-isothiocyanato-4-(methyl-sulfinyl)butane] is a natural dietary isothiocyanate isolated from broccoli and other vegetables. Sulforaphane is found to be a very potent inducer of phase 2 detoxication enzymes and other anti-oxidative capacity in cultured cells and animal models. Sulforaphane has been found to possess potent anti-carcinogenic activities and has been used as a chemo-preventive agent to forestall the development of cancers.

**Preliminary Studies**: Gene expression studies with sulforaphane exposure has demonstrated that transcriptional responses that are caused by NRF2 induction because of the covalent modification of Keap1 on its 27 cysteine residues, thus allowing NRF2 to translocate to the nucleus. Although NRF2 induction and sulforaphane have been used to boost anti-oxidative capacity and prevent many diseases, such an approach has not been applied to anemia disorders. This gap is especially surprising, given that oxidative stresses have been recognized as critical factors in the hemolysis of SCD and other anemia disorders. Based on our findings of miR-144-repression of NRF2 as a cause of compromised anti-oxidative capacity in SS RBC, we are proposing to test the potential of NRF2 induction to boost RBC anti-oxidative stress capacity and improve hemolysis and gene expression under the high level of stress seen in SCD. We believe that NRF2 induction should be regarded as distinct from anti-oxidant supplementation, since it ensures that the HbSS RBCs have enough enzyme capacity to survive stress environments instead of simply providing anti-oxidant substrates to HbSS cells that are already handicapped by insufficient anti-oxidant machinery. Furthermore, NRF2 activation also leads to the induction of HbF and epsilon forms of Hb known to inhibit the HbS polymerization and exhibit anti-sickling properties. Therefore, NRF2 activation may simultaneously have multiple benefits to reduce the hemolysis of SCD and improve clinical outcomes.

1. **Design & Procedures** –

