Study Type: This is an open label dose-escalation study to test the efficacy of daily intake of sulforaphane via broccoli sprout homogenates (BSH) to achieve the physiologically significant but non-clinical endpoint of induction of HbF, glutathione and anti-oxidative capacity in SCD erythrocytes. Each patient will serve as his/her own control, as all endpoints will be measured at pre-treatment baseline, during treatment of BSH, and post-treatment washout.

Study Population: HbSS and HbSßº thalassemia

Primary Endpoint: Safety

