Week 3 (Day 21): VS including height, weight, blood pressure, heart rate, pain, and fatigue, review of BSH intake (food diary) and concomitant medications, symptom/adverse event evaluation; medical history, review of concomitant medications, vital signs (VS), including height, weight, blood pressure, heart rate, pain, and fatigue. Venipuncture (up to 30 cc's) will be performed for CBC (complete blood count), LDH (marker for hemolysis), CMP (complete metabolic panel), baseline, HbF, SFN level, SFN-induced gene expression changes, RBC anti-oxidative capacity and gene expression.

Week 7 (Day 49, wash out): VS including height, weight, blood pressure, heart rate, pain, and fatigue, review of BSH intake (food diary) and concomitant medications, symptom/adverse event evaluation; medical history, review of concomitant medications, vital signs (VS), including height, weight, blood pressure, heart rate, pain, and fatigue. Venipuncture (up to 30 cc's) will be performed for CBC (complete blood count), LDH (marker for hemolysis), HbF, SFN level, SFN-induced gene expression changes, RBC anti-oxidative capacity and gene expression.

Participants while on the study will maintain a food diary. Each participant will receive instructions at the baseline visit on the use the food diary. The food diary data will be reviewed at each clinic visit.

The subjects who pass screening will receive sulforaphane in the form of broccoli sprout homogenates (BSH) for their intake at home daily for one week (plus 2 extra days’ supply). Subjects will return every week for the next 3 weeks of sequential visits.

1. **Selection of Subjects** –

*Inclusion Criteria*: Diagnosis of Hemoglobin (Hb) SS or Hb Sβ0 thalassemia by electrophoresis • Age ≥18 years • Hematocrit (Hct) ≥ 20% and Hb > 6.0 g/dL • Capacity to understand and sign informed consent and can adhere to the daily regimes of BSH

*Exclusion Criteria*: RBC transfusion during the 3 months prior to study entry • Pregnant• Currently receiving hydroxyurea treatments • Diabetes• Renal insufficiency (BUN >21 mg/dL and/or Creatinine >1.4 mg/dL) • History of allergy to sulfonamides

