**Risk/Benefit Assessment** – The investigators of the study do not expect the participants to receive medical benefit from their participation in this study. The tests provided may help participants learn about your general health. However, information from this study may help the investigators learn things about sulforaphane’s physiological effect on SS RBC that will help other patients with sickle cell disease in the future. This is a minimally invasive study that poses a low risk to the subject other than the general risk of loss of privacy and insertion of a venous catheter for blood draw. BSH at the doses proposed in this study have been safely used in many clinical trials for a variety of disease. Sulforaphane has a good safety profile and has been approved as broccoli sprout tea or homogenate for several human clinical trials.

1. **Costs to the Subject** – There will be no cost to subjects to participate in this study. The study will pay for the research-related items or services that are provided.
2. **Data Analysis & Statistical Considerations** –

Sample size: 50 patients for screening and 35 patients for participation. Patients will be allowed to participate in more than one dose cohort. This is a pilot study. The in vivo study in Aim 1 is designed for the participation of 6 subjects.

Primary Endpoint: Measurement of the HbF, anti-oxidative capacity, GSH and phase II enzymes and microRNA gene expression before and after the BSH injection.

Secondary Endpoints: Safety data regarding use of BSH in patients with SCD.

Descriptive statistics will be used to characterize changes from baseline in laboratory test results.

1. **Data & Safety Monitoring** – A DSMB will be established for monitoring this clinical study. DSMB members, appointed by Drs. [name] and [name], will include at least three members with expertise in hematology or oncology. The DSMB will assess the risk of this clinical trial, determine the appropriate level of data and safety monitoring, review reports of all serious adverse events (SAEs), review the regularly submitted data and safety monitoring reports, and recommend appropriate actions (e.g. closure, increased monitoring) to the PIs.

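### Sulforaphane intake from ordinary diet is neither recorded nor limited before the Day 0 sample, so a change in diet could confound changes in sulforaphane-responsive markers

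*Protocol*

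**What the plan says.** All references are to the Protocol.

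- **Diary.** Design & Procedures (study visits) states: "Participants while on the study will maintain a food diary". It then says "Each participant will receive instructions at the baseline visit on the use the food diary" and "The food diary data will be reviewed at each clinic visit". Screening/Baseline lists no diet recall. Diary review is first listed at Day 7 and continues to Day 49.
- **Source of the compound.** Background & Significance says that sulforaphane "is a natural dietary isothiocyanate isolated from broccoli and other vegetables".
- **Limits on other sources.** None is stated in the visit descriptions, Selection of Subjects or Table 1. The exclusions cover recent transfusion, pregnancy, hydroxyurea, diabetes, renal insufficiency and sulfonamide allergy.
- **Comparison.** Study Type says: "Each patient will serve as his/her own control, as all endpoints will be measured at pre-treatment baseline, during treatment of BSH, and post-treatment washout". Data Analysis & Statistical Considerations adds: "Descriptive statistics will be used to characterize changes from baseline in laboratory test results".
- **Measurements.** Table 1 marks serum SFN, glutathione, anti-stress capacity and RNA at Day 0, Day 21 and Day 49.
- **Visits.** Table 1 gives Screening and Baseline (Day 0) separate columns. The visit descriptions merge them under one Screening/Baseline heading.

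**The concern.** The study substance is a constituent of ordinary food, and the markers of interest are meant to respond to it. The sponsor regards diet as important enough to record throughout treatment and wash-out, but the record starts only when the reference sample is taken. Of the three time points that carry the comparison, Day 0 is the one with no diet record leading up to it.

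Without a control group, nothing else separates the effect of BSH from the effect of eating more or fewer other sulforaphane-containing vegetables after enrolment. Joining a broccoli-sprout study could plausibly prompt such a change in either direction. The readings at stake are the before/after marker changes, and any dose pattern across cohorts, since the same dietary shift weighs more against a small dose than a large one. Analysis cannot repair this later, because a diary that was not kept cannot be reconstructed.

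**Working it through.** **Plan's own figures.** The Protocol gives no figure for background intake, so none can be reproduced. The one usable exposure figure is 102 μmol of sulforaphane at the highest dose (Design & Procedures, below the cohort scheme).

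**Step 1: what enters the change.** Let D be the sulforaphane from BSH per day, B0 the background intake in the days before Day 0, and B21 and B49 the background intake before Days 21 and 49.

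- Exposure contrast, Day 21 against Day 0: (D + B21) − B0 = D + (B21 − B0)
- Exposure contrast, Day 49 against Day 0: B49 − B0, with no BSH in the preceding weeks

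If B21 = B0, the background drops out and the contrast is D. Only the shift matters, not the level. A fall in intake after Day 0 makes the contrast smaller than D, and a rise makes it larger. The diary can inform B21 and B49, but not B0.

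**Step 2: dose in μmol.** Assumptions: yield is proportional to grams, the 102 μmol belongs to the 200 g cohort, and the doses are daily, as Study Type describes.

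- 50 g: 102 × 50/200 = 25.5
- 100 g: 102 × 100/200 = 51
- 150 g: 102 × 150/200 = 76.5
- 200 g: 102

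**Step 3: shift as a share of dose.** The formula is |B21 − B0| / D. The shift is an assumption of 0 to 20 μmol/day; the documents give no value.

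| Cohort dose | D (μmol) | Shift 0 | Shift 5 | Shift 10 | Shift 20 |
|---|---|---|---|---|---|
| 50 g | 25.5 | 0% | 20% | 39% | 78% |
| 100 g | 51 | 0% | 10% | 20% | 39% |
| 150 g | 76.5 | 0% | 7% | 13% | 26% |
| 200 g | 102 | 0% | 5% | 10% | 20% |

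For example, 20/25.5 = 78% and 20/102 = 20%.

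**Step 4: limits of the table.** These are shares of exposure, not of marker response; the documents give no exposure-response relation. The paragraph that gives 102 μmol writes the top dose as 200 mg, while the cohort scheme and Data & Safety Monitoring write 200 g. The scaling depends on how those passages are reconciled. The Protocol also allows the 50 g dose to be adjusted, so 25.5 μmol is not fixed. The largest shares concern Cohort 1, which is 5 of 35 planned participants (5/35 = 14%).

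**The case against.** The case on the other side is substantial.

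- **Stable diet cancels.** A reader might infer that vegetables eaten before Day 0 necessarily raise the baseline and shrink the effect. Step 1 shows otherwise: intake that continues unchanged is present at both time points. Nothing in the documents shows that diets will change. This stands, and it makes the concern conditional.
- **Exposure at Day 0 is measured.** An SFN level is drawn then, so recent intake is not wholly unobserved. This stands in part. The section on the revised sulforaphane measurement says that earlier blood processing was inadequate. It requires the method to be tested before the main study, but its ability to detect ordinary background intake is not yet shown.
- **Wash-out is covered.** The diary runs to Day 49, so Days 21 to 49 are to be recorded, and Day 49 is a second off-treatment reference. This stands. However, Day 49 follows treatment, and other sources are unrestricted then too.
- **Not every endpoint is exposed.** A reader might infer that all changes from baseline are distorted. The documents do not support that. Adverse events need no dietary baseline, and the argument reaches only the markers expected to respond to sulforaphane.
- **The percentages rest on assumptions.** This stands. The range begins at zero, and dividing a habitual intake level by the dose, rather than a shift, would use the wrong quantity.
- **Low stakes.** This is a pilot with descriptive statistics, and the text contains no contradiction about the diary. Participant diet instructions could also sit in consent pages that are not shown.

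**Conclusion.** The point holds in a limited form. Under the plan as written, sulforaphane intake before the Day 0 sample is neither recorded nor restricted. In an uncontrolled within-patient design, a change in background diet between the days before Day 0 and Day 21 or Day 49 could therefore be mistaken for, or could mask, an effect of BSH on SFN level, glutathione, anti-oxidative capacity or gene expression. The sponsor would have no diet record with which to show that diet was stable.

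The size is unknown and may be nil. Under the assumptions in the working, it runs from 0 to 78% of the dose at 50 g and from 0 to 20% at 200 g, so any confounding would weigh most in the lowest cohort. This does not show that bias is present or that the safety assessment is affected. It is a minor design weakness, worth correcting because the change is cheap and the missing record cannot be recovered afterwards.

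**What to change.** 1. Issue the existing diary and its instructions at the Screening visit in Table 1, so that the days before the Day 0 draw are recorded. If Screening and Baseline are one visit, as the visit descriptions suggest, take a short diet recall before the Day 0 draw instead. State in the Protocol which arrangement applies.
2. Ask participants to avoid other broccoli, cruciferous vegetables and sulforaphane supplements from Screening to Day 49. In any case, have them record such intake in the diary.
3. Repeat the change-from-baseline summary without samples preceded by such intake. The detail can sit in the SAP.
4. Reconcile the passages that give the top dose in grams and in milligrams, so that BSH exposure can be compared with background intake.

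**Cost.** Wording changes, and an existing form handed out one visit earlier or a brief recall added. The downside is a mild diet request and slightly more recording for participants. No extra blood samples or patients are needed.

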**Preliminary sulforaphane level measurement revised procedure:**

Because our previous methods for processing blood for Sulforaphane (SFN) metabolite detection were not adequate. Four SFN metabolites: SFN-Cys, SFN-CG, SFN-NAC and SFN-GSH, should be detected in all the processed samples, yet only SFN-NAC was detected in all samples, albeit at levels so low that the amount of this metabolite could not be accurately identified with the usual standards. SFN-Cys, SFN-CG, and SFN-NAC could not be detected in any of the samples. This preliminary work is to allow optimization of the dosing preparation and the sample collection method to ensure that the amount of sulforaphane obtained from our preparation will be adequate.

We will test the ability to measure the increase of sulforaphane levels after ingestion of the non-toxic sulforaphane in a shake, smoothie, or unprocessed fresh or thawed out frozen broccoli sprouts in 20 subjects (10 subjects with sickle cell anemia and 10 healthy controls). To assess these serum levels, we must use a detailed protocol to stabilize the naturally unstable sulforaphane metabolite, and this sample must later be measured by our collaborators at the Oregon State University ([name]). We must test the efficacy of our methods before proceeding with the main study to ensure that our detailed protocol is sufficient to stabilize the metabolite in the processed samples so that our collaborators at the Oregon Health can adequately test these metabolite levels.

Participants will be asked to donate three single blood samples by peripheral intravenous draw at about 30 minutes before ingestion, 4 hours after ingestion, and 6 hours after ingestion of 100, 150, or 200 grams of BroccoSprout® Homogenate (BSH). The maximum amount of blood that will be drawn is 10 ml at each time point for a maximum of 30 ml. Participants may be asked to repeat this procedure at different levels or preparation of BSH.

Secondary Endpoint: Physiological effects – HbF, GSH, anti-oxidative capacity and the expression of Phase II enzyme expression in SS RBC.

Projected Accrual: 50 patients for screening and 35 patients for participation in study.

COHORT 1 (5 patients) – Single 50 g BSH



Review by DSMB. If Board approves,



COHORT 2 (5 patients) – Single 100 g BSH



Review by DSMB. If Board approves,



COHORT 3 (5 patients)– Single 150 g BSH



Review by DSMB. If Board approves,



COHORT 4 (20 patients)– Single 200 g BSH

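### The hydroxyurea exclusion has no look-back, unlike the transfusion exclusion, so a patient who has recently stopped can enter an uncontrolled before/after HbF study with one baseline value

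*Protocol*

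**What the plan says.** Two exclusions stand side by side in the protocol, Selection of Subjects:

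- Transfusion: "RBC transfusion during the 3 months prior to study entry".
- Hydroxyurea: "Currently receiving hydroxyurea treatments".

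The first looks back from entry; the second describes only the present. No other section sets an off-drug or stability interval for hydroxyurea. Medical history and concomitant medications are reviewed at screening/baseline and again during the study, but no eligibility rule on past hydroxyurea use is tied to that review.

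The comparison is within patient. Design & Procedures states: "Each patient will serve as his/her own control". HbF is an endpoint in both places that list endpoints. Design & Procedures has it as secondary ("Secondary Endpoint: Physiological effects – HbF, GSH, anti-oxidative capacity"), while Data Analysis & Statistical Considerations has it as primary ("Measurement of the HbF, anti-oxidative capacity, GSH and phase II enzymes and microRNA gene expression before and after the BSH injection"). The stated analysis is: "Descriptive statistics will be used to characterize changes from baseline in laboratory test results". Table 1 places HbF at Day 0, Day 21 and Day 49, with none at the screening visit.

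**The concern.** In a single-arm before/after study, the baseline value stands in for what would have happened without BSH. That works only if the patient's HbF would otherwise have stayed level over the seven weeks. A patient who stopped an HbF-raising drug days before Day 0 may not meet that condition, and the criteria as worded let that patient in.

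Nothing in the design would reveal or remove the drift. No concurrent arm shares it, and a single pre-treatment HbF value cannot show that a baseline is moving. At stake is the reading of HbF induction, one of the effects the study is set up to look for, in cohorts where three of the four have only five patients.

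**Working it through.** **Inputs from the protocol.** Cohort sizes are 5, 5, 5 and 20, and 5 + 5 + 5 + 20 = 35, which agrees with the stated number of participants. HbF is taken at Days 0, 21 and 49. BSH is dispensed at Days 0, 7 and 14, so Day 0 to Day 21 is the on-treatment comparison and Day 49 is the washout visit. The protocol gives no effect size, SD or power, so there is no planned figure to set the drift against.

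**Inputs that are assumptions.** The protocol does not say that hydroxyurea raises HbF or how fast the effect fades. The sizes below are illustrations only.

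**Linear illustration.** Assume HbF falls by D = 2 to 5 percentage points between Day 0 and Day 49 in one recently stopped patient.

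- Fall by Day 21 = D × 21/49: 2 × 21/49 = 0.86 and 5 × 21/49 = 2.14, so about 0.9 to 2.1 points.
- Shift in the mean of 5 from one such patient: -0.86/5 = -0.17 to -2.14/5 = -0.43.
- Shift in the mean of 20: -0.86/20 = -0.04 to -2.14/20 = -0.11.
- Further fall from Day 21 to Day 49: 2 - 0.86 = 1.14 to 5 - 2.14 = 2.86 points in that patient.

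**How it would read.** If BSH truly raised that patient's HbF by g points at Day 21, the observed change would be g minus 0.9 to 2.1, so a real rise of that size would appear as no change. The further fall to Day 49 would then be added to any true return after BSH stops, and the two could not be told apart.

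**Second illustration, with a decaying excess.** Let the drug-related excess be E × 0.5^((t + s)/h), with E = 5 or 10 points at stopping, half-life h = 4, 8 or 12 weeks, and s weeks between stopping and Day 0.

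- s = 0, Day 0 to Day 21: from -0.80 (E = 5, h = 12) to -4.05 (E = 10, h = 4). In a cohort of 5 the mean shifts by -0.16 to -0.81.
- s = 13 weeks, about the length of the transfusion look-back: from -0.21 to -0.75. In a cohort of 5 the mean shifts by -0.04 to -0.15.
- The share of drift left after 13 weeks is 0.5^(13/h): 0.11, 0.32 and 0.47 for h = 4, 8 and 12.

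On these assumptions, a look-back of that length removes between about half and nine-tenths of the drift, not all of it.

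**The case against.** The strongest reply is that the case rests on a patient who may never appear and a drift the documents do not quantify. Both parts are fair. The criteria permit such entry; they do not show that anyone will enter this way. The protocol gives no reason for either exclusion, so it cannot be said to treat the two as the same kind of threat. The study is also a descriptive pilot with no stated test, and Design & Procedures names safety as primary. These points limit the size and weight of the concern. They do not remove it, because eligibility is fixed in the protocol and no descriptive summary can restore a baseline that was already moving.

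A second reply is that the drift lowers HbF, so it cannot produce a false claim of induction, and a fall that continues to Day 49 is not the rise-and-return pattern of a real effect. The first half stands: for HbF, the assumed bias is towards missing an effect. The second half holds only when BSH does nothing. With a real effect partly cancelled, the pattern is ambiguous.

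A third reply is that three months suits the clearance of transfused cells and need not suit the fading of a drug effect. That stands, which is why the length should be for the investigators to justify.

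A reader might also infer that HbF and red-cell values taken after a transfusion or a hydroxyurea start during the study go uncorrected into the change-from-baseline summary. The documents do not support that. The analysis sentence does not say which values are included, and such handling is commonly left to a statistical analysis plan, which is not shown here. Leaving those values out would also have a cost of its own, since it could favour patients who stayed well.

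**Conclusion.** The concern holds as a gap in the eligibility wording. A patient who has recently stopped hydroxyurea can enter, and with no control arm and one scheduled pre-treatment HbF value, any resulting drift cannot be separated from the effect of BSH. The likely direction is to mask HbF induction at Day 21 and to mimic loss of effect at Day 49.

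The size is modest and conditional. Under the linear assumption, one affected patient moves the Day 21 mean by a few tenths of a point in a cohort of 5 and by about a tenth or less in the cohort of 20. A reader might apply the full assumed 2 to 5 point fall to the treatment effect. That would overstate it, because that fall is reached only at the washout visit. Everything rests on two assumptions from outside the documents: that HbF is still falling after hydroxyurea was stopped, and how fast it falls.

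**What to change.** - Give the hydroxyurea exclusion a look-back before study entry. The 3-month window already used for transfusion is one candidate; if the investigators prefer another interval, the protocol should state and justify it.
- State that the criterion is rechecked when a patient enters another dose cohort, since participation in more than one is allowed.
- Record time since last hydroxyurea at baseline, so that any remaining drift can be examined.

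No patient is asked to change treatment; the edit only determines who is eligible. The cost is one eligibility phrase, one data item and a slightly smaller pool of eligible patients.

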The 50 g BSH dosage may need to be adjusted to the minimal amount needed to have adequate Sulforaphane (SFN) metabolite detection.

If any serious adverse events occur, they will be reported immediately to the IRB. In addition, the study will be stopped until the DSMB reviews all available data and reaches a decision as to whether the study should be continued. The highest daily dose (200 mg) to be used in this study has been safely used in a previous trial. This dose will yield 102 μmol of sulforaphane. An escalating dose design is used in this study to monitor for safety in patients with sickle cell disease; also, previous studies show significant dose dependent increase on the response to BSH with greater response at the higher dose of 200 mg/day.

Study visits:

Screening/Baseline:

informed consent verification, medical history, review of concomitant medications, vital signs (VS), including height, weight, blood pressure, heart rate, pain, and fatigue. Venipuncture (up to 30 cc's) will be performed for CBC (complete blood count), LDH (marker for hemolysis), CMP (complete metabolic panel), baseline, hemoglobin electrophresis, HbF, Hb A2, SFN level, SFN-induced gene expression changes, RBC anti-oxidative capacity and gene expression.

Week 1 (Day 7): VS including height, weight, blood pressure, heart rate, pain, and fatigue, review of BSH intake (food diary) and concomitant medications, symptom/adverse event evaluation and continue food diaries; physical exam, vital signs (BP, pulse, temperature, height, weight, pain, and fatigue), review of concomitant medications. Venipuncture (up to 30 cc's) will be performed for CBC, LDH, SFN level. Review of food/fluids intake. Collection of sulforaphane supplement returned.

Week 2 (Day 14) VS including height, weight, blood pressure, heart rate, pain, and fatigue, review of BSH intake (food diary) and concomitant medications, symptom/adverse event evaluation and continue food diaries; physical exam, vital signs (BP, pulse, temperature, height, weight, pain, and fatigue), review of concomitant medications. Venipuncture (up to 30 cc's) will be performed for CBC, LDH, SFN level. Review of food/fluids intake. Collection of sulforaphane supplement returned.

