All SAEs will be reported to the IRB, and the DSMB. The DSMB will review these data and notify the PI if safety appears to be an issue. If there are significant adverse events, the DSMB may recommend that the study be terminated. DSMB meetings for review of study data and decision of continuation will be scheduled as follows: after five patients complete the study at each dose level for cohort 1, 2, and 3; after twenty patients complete the study the 200 g dose level; or at any other times as deemed necessary by either the PI or any of the DSMB members.

1. **Privacy, Data Storage & Confidentiality** – The privacy rights of the subjects will be protected as required by law. All information that can identify an individual and the individual medical history will be kept confidential within the limits of the law. All study information will be kept locked in file cabinets accessible only by clinical research staff that are authorized and IRB-approved to participate in the study. Electronic information will be stored in secure electronic systems accessible only by Drs. [name] and [name], and their clinical research team.

Table 1. Study Related Tests and Procedures

| Procedures | Screening Visit | Baseline (Day 0) | Day 7 | Day 14 | Day 21 | Day 49  (Wash out) |
| --- | --- | --- | --- | --- | --- | --- |
| Informed Consent | X |  |  |  |  |  |
| Clinic Visit | X | X |  |  | X | X |
| Interview to identify AE’s |  | X |  |  | X | X |
| Vital Signs | X | X |  |  | X | X |
| Physical Examination | X | X |  |  | X | X |
| MD screen, history | X | X |  |  | X | X |
| BSH dispensed |  | X | X | X |  |  |
| **Clinical Laboratory Tests** |  |  |  |  |  |  |
| Venipuncture | X | X |  |  | X | X |
| Complete Blood Count (CBC) | X | X |  |  | X | X |
| Reticulocyte count | X | X |  |  | X | X |
| LDH (marker of hemolysis) | X | X |  |  | X | X |
| Comprehensive Metabolic  Profiling (CMP) |  | X |  |  | X |  |
| Hemoglobin electrophoresis |  | X |  |  |  |  |
| HbF quant |  | X |  |  | X | X |
| Serum SFN level |  | X |  |  | X | X |
| **Research Studies** |  |  |  |  |  |  |
| Glutathione |  | X |  |  | X | X |
| Anti-stress capacity |  | X |  |  | X | X |
| Reactive Oxygen Species |  | X |  |  | X | X |
| RBC/Reticulocyte RNA |  | X |  |  | X | X |
| PAXgene whole blood |  | X |  |  | X | X |

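### Day 7 and Day 14 are assessed safety visits in the protocol text but dispensing-only contacts in Table 1

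*Protocol*

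**What the plan says.** The Study visits part of Design & Procedures describes Week 1 (Day 7) and Week 2 (Day 14) in the same terms. Each includes vital signs, a review of BSH intake and concomitant medication, and "symptom/adverse event evaluation and continue food diaries; physical exam, vital signs (BP, pulse, temperature, height, weight, pain, and fatigue". At each visit venipuncture "will be performed for CBC, LDH, SFN level". The closing paragraph of that section confirms weekly attendance: "Subjects will return every week for the next 3 weeks of sequential visits".

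Table 1 (Study Related Tests and Procedures) has columns for Screening, Day 0, Day 7, Day 14, Day 21 and Day 49. In the assessment rows the Day 7 and Day 14 cells are empty:

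- "Clinic Visit | X | X | | | X | X"
- "Interview to identify AE’s | | X | | | X | X"
- "Complete Blood Count (CBC) | X | X | | | X | X"
- "Serum SFN level | | X | | | X | X"

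The only row marked on those two days is the supply row: "BSH dispensed | | X | X | X".

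**The concern.** Staff cannot comply with both schedules, and the protocol has no footnote or precedence rule to settle the matter. Schedule tables are commonly what a clinic works from. This one reads as a coherent design in which patients collect supplies at Day 7 and Day 14 and are assessed only at Day 21, so a reader of the table has no cue to check the text.

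What is at stake is on-treatment safety information. Design & Procedures explains the escalating doses partly by the need to monitor safety in patients with sickle cell disease. It also halts the study on any serious adverse event until the DSMB has reviewed the data. Under Data & Safety Monitoring, the DSMB reviews each of cohorts 1 to 3 once five patients have completed. If Table 1 is followed, no question about adverse events and no blood count is scheduled while the three weekly supplies are being handed out. During that time the halt would depend on patients reporting problems themselves.

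The planned description of laboratory change from baseline suffers too. CBC, LDH and SFN level would each have one on-treatment value instead of three.

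**Working it through.** The protocol gives no figure to reproduce here. The check sets the two schedules side by side and counts. No event rate or event timing is assumed.

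**Step 1. Conflicting cells at Day 7 and Day 14.**

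| Item | Study visits text | Table 1 |
|---|---|---|
| Clinic visit | yes, both days | blank, both days |
| Adverse event evaluation | yes, both days | blank, both days |
| Vital signs | yes, both days | blank, both days |
| Physical examination | yes, both days | blank, both days |
| Venipuncture | yes, both days | blank, both days |
| CBC | yes, both days | blank, both days |
| LDH | yes, both days | blank, both days |
| Serum SFN level | yes, both days | blank, both days |

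Conflicting cells: 8 rows × 2 days = 16.

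**Step 2. Could the blanks be a fault of text extraction?** The supply row carries marks at Day 0, Day 7 and Day 14, in the expected columns. The assessment rows carry marks at Day 21 and Day 49, with the two empty cells in the same position each time. The columns are therefore intact and the blanks are real.

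**Step 3. Scheduled adverse event evaluations after the first dose, per patient.**

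- Text: Days 7, 14, 21 and 49, so 4 in all and 3 through Day 21.
- Table 1: Days 21 and 49, so 2 in all and 1 through Day 21.
- Longest interval without an evaluation from Day 0 through Day 21: 7 days (text) against 21 days (Table 1).

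CBC, LDH and SFN samples follow the same pattern: 4 against 2 after the first dose, and 3 against 1 through Day 21.

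**Step 4. The same difference by cohort and overall.** These are multiples of Step 3, given for scale only.

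- Five-patient cohort, through Day 21: 5 × 3 = 15 against 5 × 1 = 5.
- Five-patient cohort, through Day 49: 5 × 4 = 20 against 5 × 2 = 10.
- All cohorts: 5 + 5 + 5 + 20 = 35 places. Through Day 21: 35 × 3 = 105 against 35 × 1 = 35, a difference of 70.

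**The case against.** The contradiction itself is hard to dispute. The case on the other side is that it matters less than it seems.

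- **The escalation gate is unchanged.** The DSMB meets after five patients complete, so under either schedule it has Day 21 and Day 49 adverse event and CBC/LDH data. This stands. What changes is how much on-treatment data each review holds.
- **A Day 21 interview can cover the whole period since Day 0.** This is largely right for adverse events, so half the evaluations does not mean half the information. What is lost is timeliness and some recall. Interim CBC, LDH and SFN values cannot be recovered later.
- **Serious events are reported immediately in any case.** Patients have study telephone numbers (Consent Process), and the DSMB can meet at any time. The halt is therefore weakened, not disabled.
- **The product is low risk.** The Risk/Benefit Assessment says these doses have been used safely in many trials. That bears on severity, not on which schedule applies.
- **The endpoint wording does not settle it.** Design & Procedures names safety as the primary endpoint, but Data Analysis & Statistical Considerations lists it as secondary. The statement that endpoints are measured during treatment is also met by Day 21 alone. This is correct, so the case for the text rests on the explicit Day 7 and Day 14 paragraphs and the weekly-return sentence.
- **Marking 16 cells leaves other mismatches.** Table 1 has physical examinations at Screening, Day 0, Day 21 and Day 49, while the text lists one only at Days 7 and 14. The reticulocyte count appears only in the table. The text merges Screening and Baseline. This is fair, and the fix below allows for it.

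**Conclusion.** The concern holds. The text and Table 1 contradict each other in 16 cells, and the protocol does not say which governs. This is more than clerical, because following the table moves the first scheduled on-treatment adverse event question and blood count from Day 7 to Day 21, after the last supply has been issued. Per patient, adverse event evaluations through Day 21 fall from 3 to 1, as do CBC/LDH/SFN samples.

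The harm is conditional: it arises only if staff work from Table 1. The counts assume three weekly supplies, issued as Table 1 marks them, and every scheduled visit attended. The point should be corrected before enrolment. It does not invalidate the design.

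**What to change.** In Table 1, mark Clinic Visit, the adverse event interview, Vital Signs, Physical Examination, Venipuncture, CBC, LDH and Serum SFN level at Day 7 and Day 14, 16 cells in all. While the table is open, reconcile the remaining mismatches (physical examination, reticulocyte count, Screening versus Baseline) and add a sentence saying which source governs if the two differ.

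Optionally, require the adverse event interview to come before resupply at Day 7 and Day 14. This is a new rule, but it only orders steps within a visit the text already requires.

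If dispensing-only weeks were intended, amend the Study visits text instead and state how adverse events will be asked about at dispensing. That choice protects patients less.

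Cost of marking the 16 cells: nothing relative to the text. Relative to Table 1, it adds two assessed visits and up to 2 × 30 = 60 cc of blood per patient, or 35 × 2 = 70 visits over the 35 places.
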